# Impact of simulation-based training in addition to theoretical training versus theoretical training of nurses alone in the occurrence of adverse events related to arteriovenous fistula puncture in chronic hemodialysis patients: study for a cluster randomized controlled trial (SIMFAV2)

**DOI:** 10.1186/s13063-023-07513-8

**Published:** 2023-08-07

**Keywords:** Adverse events, Arteriovenous fistula, Nurse, Simulation, Simulation-based training

## Abstract

**Background:**

The technique of arteriovenous fistula (AVF) puncture is currently taught by colleagues within hemodialysis units. Even if the main principles of the technique are well known and common to all hemodialysis units, strong rationales are still missing to standardize fine practices such as the relative position of the needles, the angle of the needle at puncture, and the position of the bevel at the time of puncture and after the needle is in the vascular lumen.

**Methods:**

We are conducting a prospective, comparative, center-randomized, multicenter study involving 8 hemodialysis centers. The primary objective is to compare the number of adverse events related to AVF puncture between a group receiving theoretical training plus simulation-based training (4 centers) and a group receiving only theoretical training (4 centers). The study will include all adult patients who are scheduled to have an AVF puncture performed by a hemodialysis-trained nurse during a scheduled chronic dialysis session.

**Discussion:**

We hypothesize that a training program for nurses on the AVF approach in procedural simulation versus theoretical input alone would decrease the adverse events related to AVF punctures and would be beneficial for the patient. This study is innovative for several reasons. First, simulation-based training in continuing education among professionals is not widely used. Furthermore, training allows for the standardization of practices within the team, both technically and relationally.

**Trial registration:**

ClinicalTrials.gov NCT05302505. Registered on March 17, 2022.

## Introduction

### Background and rationale {6a}

Chronic renal failure refers to a decrease in the purification function of the kidneys. When chronic renal failure reaches the end stage, only the implementation of renal replacement therapy allows the affected subjects to stay alive. Three types of replacement therapy are offered to patients with end-stage renal disease: transplantation, extrarenal purification by peritoneal dialysis, and extrarenal purification by hemodialysis (HD).

### Hemodialysis

Hemodialysis is the first modality of treatment in France [1]. It is a technique of purification of uremic toxins accumulated in the blood of patients via extracorporeal circulation and a semipermeable membrane. This treatment requires specific technical skills from the nephrology service providers who are in charge of it. There are four basic elements to consider when performing hemodialysis treatment: the vascular approach, the extracorporeal circulation circuit in which the patient’s blood circulates, the artificial kidney or dialyzer, and the HD machine. The quality of the treatment depends largely on the quantity of blood that can be treated during the hemodialysis session and therefore on the quality of the vascular approach from which the blood is extracted and returned to the patient. There are two types of vascular access, central venous catheter and arteriovenous fistula (AVF), which is the preferred type of access.

### Arteriovenous fistula

AVF is a communication between an artery and a superficial vein, which is created surgically, and after a maturation period of at least 6 weeks, it allows us to obtain a portion of the superficial vein of good caliber in which the blood flow is sufficiently important to allow the realization of hemodialysis. The AVF must be punctured by a nurse at each session with two large gauge needles to allow sufficient blood flow. This step, which is repeated more than 300 times a year per patient, is crucial to the success of the treatment. The quality of its execution determines the success of the treatment [2]. This procedure requires specific skills [3] to prevent the many complications that can arise from incorrect positioning of the needle in the AVF lumen, pain, hematoma at the puncture site, false aneurysm or pulsatile hematoma, transfixing puncture of the vein, infection, scarring, and even necrosis at the puncture site with a risk of unpredictable AVF rupture and cataclysmic acute bleeding [4].

The psychological aspect must be taken into account, as difficult or even painful punctures often cause apprehension in patients, even real anxiety, and can be a source of deterioration in quality of life.

Finally, the quality of the AVF puncture also impacts the quality of the treatment [5]. In the case of malposition of the needles in the vascular lumen, the blood flow and thus the quantity of blood treated can be greatly reduced. A more severe puncture complication may render the vascular approach unusable for several days [6].

The population of subjects treated in hemodialysis is made up of increasingly older patients with vascular comorbidities and often diabetes. All these factors negatively influence the quality of the vessels for AVF preparation and contribute to increasing the risk of complications related to AVF puncture.

### AVF puncture technique

Currently, the technique of AVF puncture is taught by colleagues within hemodialysis departments. The contribution of a training program on the approach to AVF in procedural simulation seems to be relevant [7]. Although the main principles of the technique are well known and common to all hemodialysis units, strong rationales are still lacking to standardize fine practices such as the relative position of the needles, the angle of the needle at puncture, and the position of the bevel at the time of puncture and after the needle is in the vascular lumen. This technique has not yet been precisely protocolized. The empirical observations made in the centers show complications of AVF puncture. These could probably be avoided by improving the quality of the puncture [8].

Thus, the standardization of the AVF puncture technique could be part of a process of optimization of practices and continuous improvement of care [9].

Procedural simulation appears to be an interesting tool to ensure the conceptualization of the AVF approach.

### Procedural simulation

The term Simulation in Health refers to the use of hardware (such as a mannequin or procedural simulator), virtual reality, or a standardized patient, to replicate care situations or environments, for the purpose of teaching diagnostic and therapeutic procedures and rehearsing processes, medical concepts, or decision-making by a health care professional or team of professionals. According to the French Health Authority, health care simulation is intended for all health care professionals and allows training in procedures, the management of situations, acquiring and updating technical and nontechnical knowledge and skills, and analyzing professional practices with debriefings [10].

Simulation-based teaching allows students to learn from experience, develop individual skills [11], and know and apply procedures in continuing education. However, it is not widely used, although it could be used to update knowledge of procedures and to harmonize practices that have been transmitted from one nurse to another. It allows professionals to adapt to new practices and recommendations and to acquire new knowledge and skills to serve the patient [12]. Simulation-based learning can also accompany other forms of simulation, such as training AVF on a simulated patient wearing a procedural simulator (hybrid simulation) [13].

The notion of performance implies the concept of evaluation in simulation. This can be based on the performance of the trainee but also on the evaluation of the training itself, according to the Kirkpatrick model [14, 15], the reference model for evaluation. Level 1 measures the degree of satisfaction of the learner. Level 2 is a pedagogical evaluation that measures what the learner has learned. Level 3 assesses how the learner modifies a procedure in a given scenario. The first three levels are directly related to the impact on the learner. The last level measures the direct benefit to the patient. It looks at the benefits of the training in the real world: what the changes did for the patient.

Studies have been carried out on the impact of simulation training on performance or on the reduction of iatrogeny, particularly during the continuing education of professionals. In the study by Mac Master et al. [16] on the “removal of fish hooks” in emergency departments, it was shown that after a training program including simulation, the hooks were removed without complications. Regarding anesthesia, Bruppacher et al. [17] showed that training through simulation versus interactive seminars increased the care performance of senior physicians at the end of extracorporeal circulation procedures in the operating room. Finally, in a recent study, Ajmi et al. [18] showed that after a hybrid simulation training program on the management of stroke patients, the time from admission to fibrinolysis, as well as the number of patients with a poor vital prognosis, was reduced. All of these studies show real benefit in patient management.

The review of the literature does not show a consensus on how to approach AVF or how to teach the procedure. Thus, we conducted a feasibility, monocentric, prospective, observational, before/after simulation training pilot study, SIMFAV (NCT03680209), at the University Hospital of Caen (unpublished data). We proposed a program with the help of nephrology nurses from a hemodialysis unit, nephrologists, a medical hypnosis practitioner, an ultrasound paramedic, and health simulation educators. We contend that the technical nature of the AVF puncture procedure must not overshadow health care providers’ relationship with the patient. Communication must be an integral part of technical care for the global care of the patient. Thus, the training program proposed in this study includes training in therapeutic communication with a hybrid simulation workshop (AVF puncture with a simulated patient). The results showed a decrease in complications (Kirkpatrick 4), such as a reduction in observed hematomas (*p* = 0.001) and a reduction in pain intensity (*p* = 0.03).

Therefore, we propose the SIMFAV2 study, a multicenter, randomized, comparative study between a group of providers that received only theoretical training and a group that received theoretical training and procedural simulation training.

## Objectives {7}

We hypothesize that a training program for nurses on AVF approach in procedural simulation versus theoretical input alone would decrease the adverse events related to AVF punctures and would be beneficial for the patient. As the patient’s management is not modified, only the consequences of the optimization of the procedure will be evaluated through the collection of the number of adverse events occurring during AVF puncture.

The primary objective was to compare the number of adverse events related to AVF puncture between a group receiving theory- and simulation-based training (TTST) and a group receiving only theoretical training (TT).

There were secondary objectives that were to compare the TTST and TT groups: occurrence of other adverse events related to AVF puncture during a hemodialysis session, patients’ experience of pain and anxiety, and nurses’ behavioral changes in medical device use.

## Trial design {8}

This is a prospective, multicenter cluster randomized controlled trial.

All centers use the same types of medical devices (catheters and puncture needles) and have an ultrasound machine available on site. The number of daily punctures varies from 13 to 40 depending on the center. A center effect will be sought.

Only two centers have a lower number of patients and punctures, but they are still comparable. We therefore propose to match the centers according to number of patients and punctures per day. We grouped the centers into pairs according to the criteria of number of AVF punctures per day, number of nurses, before randomization.

The different experimental and control groups will move forward in pairs (e.g., center A of the experimental group, center A of the control group).

The trial design is described in Fig. 1.

**Fig. 1 Fig1:**
[figure not shown]
Trial design

## Methods: participants, interventions, and outcomes

### Study setting {9}

This study involves 8 hemodialysis centers in a French district, the Normandy. We called for volunteers to take part in the study. Among participating centers, there are the community centers of Dieppe, Mémorial France Etats-Unis of Saint-Lô, Lisieux; the nonprofit centers “ANIDER” of Alençon, Hérouville Saint-Clair, Flers and Dieppe; and a private hospital Saint Martin of Caen.

There will be approximately 140 nurses participating in this study. They will complete a data collection on the occurrence of adverse events. An anonymity number will be assigned to each participating nurse.

The start of the study for each center will be staggered by 1 month to allow for the distribution of training.

Data are collected in each hemodialysis centers and then centralized in the Caen University Hospital.

### Eligibility criteria {10}

All patients aged over age 18 scheduled for AVF puncture by a hemodialysis-trained nurse during a scheduled chronic dialysis session were eligible.

All dialysis nurses puncturing the included patients will be included in the study.

#### Criteria for non-inclusion

Patients who met the following criteria were excluded: having an AVF puncture in the emergency unit, refusing data collection, not speaking French, being less than 18 years old, being under guardianship or unable to give informed consent, being enrolled in a social security plan, being pregnant, or breastfeeding.

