### Recruitment {15}

All patients received hemodialysis in the center, excluding those who needed emergency care. There are between 17 and 34 punctures per day. Target sample sizes are not difficult to achieve.

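### The non-inclusion list, as printed, excludes patients who are enrolled in a social security plan; the criterion appears to have lost a negation and does not fit the rest of the protocol

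*Protocol article*

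**What the plan says.** The section on criteria for non-inclusion opens with a governing clause, "Patients who met the following criteria were excluded", and ends its list with "being under guardianship or unable to give informed consent, being enrolled in a social security plan, being pregnant, or breastfeeding". Enrollment in a social security plan is therefore itself a reason to exclude.

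Three other places describe who enters the study:

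- The abstract's methods paragraph: "The study will include all adult patients who are scheduled to have an AVF puncture performed by a hemodialysis-trained nurse".
- Eligibility criteria {10}: "All patients aged over age 18 scheduled for AVF puncture by a hemodialysis-trained nurse during a scheduled chronic dialysis session were eligible".
- Recruitment {15}: "All patients received hemodialysis in the center, excluding those who needed emergency care", followed by "Target sample sizes are not difficult to achieve".

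None of these mentions insurance status, and no other section of the article mentions it or corrects the criterion.

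**The concern.** The direction of the criterion looks inverted. Insurance status is the only item on the list that has no evident reason to exclude a patient when worded in this direction. Nothing in the rationale or design suggests that the study is meant for uninsured patients.

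This sentence defines who may be included; it is not background text. If it were followed as printed, insured patients would be left out. If staff followed the presumed intent instead, each insured patient they included would formally breach the published criterion. The section on the data monitoring committee {21a} has a review committee grade protocol deviations as minor or major, and data are excluded for major ones. The same section keeps all data in the intention-to-treat analysis, apart from cases of absent or withdrawn consent. The exposure is therefore in the deviation count, and in any analysis that drops major deviations.

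**Working it through.** No formula applies, and the plan gives no figure to reproduce. The check is a comparison of the texts.

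**1. Grammar of the list.** The governing clause says that meeting a criterion leads to exclusion. Every other item is worded as the condition that excludes: puncture in the emergency unit, refusal of data collection, not speaking French, age under 18, guardianship or inability to consent, pregnancy, breastfeeding. The language item and the inability-to-consent item show that the sentence uses a negative form where one is meant. List style therefore does not explain its absence from the social security item. Read by the same rule as its neighbors, that item excludes the enrolled.

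**2. Comparison with the inclusion statements.**

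| Place | Who is in | Insurance restriction |
|---|---|---|
| Abstract, methods | All adults scheduled for a nurse-performed fistula puncture | None |
| Eligibility criteria {10} | All patients over 18 at a scheduled chronic session | None |
| Recruitment {15} | All in-center hemodialysis patients except emergency care | None |
| Criteria for non-inclusion | Those not meeting a listed condition | Enrolled patients removed |

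The last row departs from the other three on insurance status.

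**3. Comparison with the feasibility claim.** The sample size section plans 600 punctures per center before training and 600 after it, and the recruitment section says "Target sample sizes are not difficult to achieve". That statement sits comfortably with a rule that removes few patients. It does not sit with a rule that removes insured patients, if these are a large part of the dialysis population.

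**4. What cannot be computed.** The share s of otherwise eligible patients who are enrolled is not stated. A literal reading leaves a fraction 1 − s, and on the documents alone s may lie anywhere from 0 to 1. The setting is given ("This study involves 8 hemodialysis centers in a French district, the Normandy"), but the article attaches no enrollment figure to it.

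**The case against.** **Exclusions always narrow a general statement.** The eligibility sentence says who is eligible in general, and the next heading lists exceptions. The language, guardianship and pregnancy items cut into the general statement too. This stands: having an exclusion list is not a contradiction. What remains is the direction of one item and how many patients it might remove.

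**This may be only a misprint in the article.** The trial runs under protocol version V03_30.06.2022, recruitment began in September 2022, and the full protocol and screening forms are not shown. This also stands. The document cannot show that the error reached the centers, and for that reason the remedy begins with a check.

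**Stronger readings that a reader might infer.**

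- *A calculated shortfall in punctures.* One could assume that 90% of patients are enrolled and compare what is left over 28 days with the 600 planned. The 90% has no source in the documents. The comparison also fails to isolate this criterion. At the low end of the recruitment section's range, 17 × 28 = 476, and at the low end of the trial design section's range, 13 × 28 = 364. Both are below 600 with no insurance exclusion at all.
- *Imbalance between arms.* One could argue that centers read the rule differently and so produced different patient mixes in the two groups. Nothing in the article shows that any center applied the wording literally, or that centers differed. This is conjecture.

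**Conclusion.** Wrong as written. The published criterion excludes patients enrolled in a social security plan, which does not fit the abstract, the eligibility section or the recruitment section. A dropped negation is the most plausible explanation. That is an inference from the sentence and its context, because the article nowhere states the intended direction.

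The size is undetermined: neither the share of patients affected nor the practice in the centers is given. If the error is confined to the article, the primary outcome, sample size, allocation and analysis are untouched. If it was carried into the screening documents, it affects who was included. The correction should be made, because the sentence is an eligibility rule and no other text in the article repairs it.

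**What to change.** 1. Compare the sentence with the full protocol, version V03_30.06.2022, and with the screening instructions and case report form in use at all 8 centers.
2. Correct the criterion to the intended direction, presumably that patients who are not enrolled in a social security plan are excluded, and make it agree with the abstract, Eligibility criteria {10} and Recruitment {15}.
3. Confirm from screening and deviation records that no patient was turned away, or recorded as a deviation, because of the literal wording. If any was, report the number by center and arm.

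The wording change is a word or two, plus a check of the forms and records. The article appeared in August 2023 and recruitment was expected to finish by March 2024, so on the stated dates the check could be made while recruitment was still open. No change to design, sample size or analysis is needed.

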### Who will take informed consent? {26a}

The coordinating investigator will give eligible participants a detailed oral and written description of the study. An opportunity to ask questions will be provided before written informed consent is obtained.

### Additional consent provisions for collection and use of participant data and biological specimens {26b}

N/A. There are no planned ancillary studies involving the collection of data for purposes separate from the main trial. No additional biological samples will be collected for use in future studies.

## Interventions

### Explanation for the choice of comparators {6b}

Currently, with the advent of the digital age, access to e-learning courses, sometimes free of charge, is easy. To evaluate the effectiveness and usefulness of the procedural simulation itself, we will compare two groups of professionals: one receiving theory training in e-learning and simulation-based training and a group receiving only theoretical training in e-learning.

### Intervention description {11a}

Interventions for each group with sufficient detail to allow replication, including how and when they will be administered.

### Control arm (TT)

This group of nurses will benefit from a theoretical distance learning program that is based on the following:Rules of hygiene, asepsis, and operator protection, in accordance with good practice [27, 28]Optimal approach to the AVF: spotting, palpation, examinationEffective fixation of the catheterBasic principles of therapeutic communicationBasic principles of ultrasound and operation of the ultrasound machineUltrasound identification/guidance of the AVF

At the end of the training program, nurses will be evaluated with a minimum passing score of 90%. Otherwise, nurses have to repeat the program until they achieve a satisfactory score, according to the principle of “mastery learning”, within the time limit of 1 month after the start of the training. Immediate feedback will be provided.

### Experimental arm (TTST)

#### First phase: theoretical training

This group of nurses will receive the same theoretical distance learning program as the experimental group. A notification of the success of the evaluation will be sent by the trainer to the promotor to begin the posttraining data collection phase.

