#### Second phase: simulation-based training

The training at the next center starts at the end of the training of the previous center (duration per center: approximately 2 months).

The simulation-based training program is based on the pedagogical strategies described in simulation and seems to be relevant in this context, i.e., deliberate practice, mastery learning, and rapid cycle deliberate practice.

Peyton’s “4 steps” method is used for new learning. We will propose a variation of this learning tool that is more adapted for a group.

A “minimum passing score” (MPS) will be established on the main steps necessary to perform the procedure, including respect for good hygiene practices and effective communication. If the MPS is not reached, the learner can repeat the different workshops until an acceptable score is obtained (90% of correct answers).

The training will take place on a procedural mannequin, that is, an arm with a pulsatile AVF that is echogenic.

The training also includes a scenario with simulated patients using the “rapid cycle deliberate practice” method [19]. It is relevant to work on communication with the patient during procedural simulation.

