### Strategies to improve adherence to interventions {11c}

To ensure the motivation of the nurses in the control group, they will receive simulation-based training once all the data needed for the study have been collected.

Additionally, nurses are thanked for their participation in the whole study with a culture voucher of a total value of 100 euros. These vouchers will be distributed to the nurses who complete the entire study (pretraining, training, and posttraining survey).

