
The same number of 4800 punctures for the T5 period (baseline) is also used. This means a total of 9600 punctures over the study period.

Several levels are taken into consideration: center, nurse, patient, and AVF puncture. Within a single center, the overall reflection of activity is related to history, practices, schedules, recommendations, etc. This center-specific activity may differ from one center to another. The experience of the nurses led to the same effects from one center to another, such as the characteristics of the patients and the AVF. These different points are taken into consideration to look for possible differences and effects that could be the cause of confounding factors.

In total, 8 centers participated, with 600 pretraining punctures per center and 600 posttraining punctures per center; that is, 9600 punctures were observed.

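### As worded, post-training data collection in the simulation arm opens when nurses pass the e-learning test, before the simulation phase, and no other start rule is given for that arm

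*Protocol article*

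**What the plan says.** All references are to the protocol article.

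- **Trigger.** Experimental arm (TTST), First phase: theoretical training: "A notification of the success of the evaluation will be sent by the trainer to the promotor to begin the posttraining data collection phase". The sentence before it reads: "This group of nurses will receive the same theoretical distance learning program as the experimental group".
- **E-learning test.** Control arm (TT) sets a pass mark of 90%, to be reached "within the time limit of 1 month after the start of the training".
- **Simulation.** Second phase: simulation-based training has its own 90% pass mark, but no notification and no start of collection attached to it. On rollout it says: "The training at the next center starts at the end of the training of the previous center (duration per center: approximately 2 months".
- **Order of phases.** Strategies to improve adherence reserves the vouchers for "nurses who complete the entire study (pretraining, training, and posttraining survey". Sample size plans "600 pretraining punctures per center and 600 posttraining punctures per center".
- **Timing between centres.** Study setting: "The start of the study for each center will be staggered by 1 month to allow for the distribution of training". Trial design: "The different experimental and control groups will move forward in pairs".

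**The concern.** The trial isolates the effect of simulation by adding it to e-learning that both arms receive. TTST post-training data are informative only if the nurses have already been through simulation. The one sentence that says when those data start to be collected stands in the theory phase and refers to an evaluation that, at that point in the text, can only be the e-learning test. Staff who follow it would open collection when TTST nurses have had the same training as control nurses. Punctures counted in that interval contribute no contrast between the arms and pull the estimated effect towards zero.

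A smaller matter is that the text does not show how the stagger of study start, the sequence of training and the pairing of centres fit together. The relative timing of the windows within a pair therefore cannot be read from it.

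**Working it through.** **1. Which evaluation triggers collection?** Up to the trigger sentence, the only evaluation described is the e-learning test (Control arm). The simulation pass mark appears afterwards, under the second phase. The visible text gives no other start rule for TTST post-training collection, and none for the control arm.

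**2. How long is the post-training window?** Inputs: 600 post-training punctures per centre (Sample size); 13 to 40 punctures per day (Trial design) or 17 to 34 (Recruitment). Days = 600 / punctures per day.

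- 600/40 = 15.0 and 600/13 = 46.2 days
- 600/34 = 17.6 and 600/17 = 35.3 days

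Training takes about 2 months per centre, roughly 60 days. Every one of these windows is shorter.

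**3. What share f of TTST punctures could precede simulation?** The documents do not give f. As an illustration, assume collection and simulation start together and nurses are trained at an even rate over L days, with a window of d days. Then f = 1 − d/(2L) if d ≤ L, and f = L/(2d) if d > L.

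- L = 60 (the 2 months are simulation alone): 1 − 46.2/120 = 0.62 to 1 − 15/120 = 0.88
- L = 30 (the 2 months include 1 month of e-learning): 30/(2 × 46.2) = 0.33 to 1 − 15/60 = 0.75

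f is 1 if the window closes before the first session. It is near 0 if sessions are bunched at the start: 140/8 = 17.5 nurses per centre, at 4 to 6 per one-day session, need only 3 to 5 sessions. It is 0 if collection in fact starts after simulation.

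**4. Effect on the contrast.** Planned rates are 9.3% and 4.65% (Sample size). Assume e-learning alone equals control. TTST rate = 9.3% × [1 − 0.5(1 − f)]; observed relative reduction = 50% × (1 − f). The number per arm is for 90% power, two-sided 5%, pooled two-proportion formula, no clustering.

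| f | TTST rate | Observed reduction | n per arm |
|---|---|---|---|
| 0 | 4.65% | 50% | 629 |
| 0.25 | 5.81% | 37.5% | 1205 |
| 0.5 | 6.98% | 25% | 2905 |
| 1 | 9.3% | 0% | nothing to detect |

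The plan has 2400 punctures per group. This formula does not reproduce the plan's pre-inflation total of 610, since it gives 629 per arm. That is a separate matter and nothing here depends on it.

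**5. Timing between centres.** The stagger concerns the start of the study; the 2-month sequence concerns the start of training.

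- Stagger per pair: pairs start at months 0, 1, 2, 3, but back-to-back training starts at 0, 2, 4, 6. The wait before training grows by 1 month per pair.
- Stagger per centre, arms alternating: the eight centres start at months 0 to 7 and the TTST centres at 0, 2, 4, 6. This fits the 2 months, but the two centres of a pair start 1 month apart.
- E-learning counted within the 2 months, with only the simulation blocks running back to back: this also fits a 1-month stagger, but the text puts the 2 months under the simulation phase.

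**The case against.** The strongest reply is that this is a slip of drafting. The paragraph is visibly garbled: it tells the experimental arm that it gets the same programme as the experimental group, so it may have been written for the control arm. Elsewhere the order is pretraining, training, posttraining, and for TTST nurses training has two phases, so posttraining naturally means after simulation. The time points T5 and T8 are used as if defined, and the trial-design and timeline figures, which may define them, are not shown. All of this stands. A reader might infer that TTST outcomes will in fact be collected before simulation; the documents do not support that. What remains is that the sentence is the only start rule in the text, and as written it is wrong.

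A reader might also infer that the timelines contradict each other. They do not strictly do so, because the 1 month and the 2 months refer to different events and a per-centre stagger can accommodate both.

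Nor can dilution be added to a calendar-time imbalance between arms. Dilution requires TTST collection before simulation. The imbalance requires TTST collection after simulation with control collection straight after e-learning, and no passage says that control collection opens then; the 1 month is a limit for passing the test.

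**Conclusion.** The point holds as a misplaced operational rule that must be corrected. As worded, TTST post-training collection opens on success in e-learning, before simulation, and the visible text offers no alternative rule. The most likely cause is drafting, and under the probable intention f = 0 and nothing is lost. If the rule were followed, the window of about 15 to 46 days is short enough against about 2 months of training for much or all of the TTST sample to precede simulation. The dilution figures rest on an assumed f, on e-learning alone being equal to control, and on no clustering; they show sensitivity and predict nothing. The timing passages are unreconciled and carry less weight.

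**What to change.** - Move the TTST trigger to the end of the second phase: post-training collection opens once the centre's nurses have passed the simulation evaluation. Correct the arm label in the same paragraph.
- State one start rule for each arm.
- Open the post-training window in both centres of a pair over the same calendar period. Keep the delay since e-learning the same in both, for example by running e-learning at the same time in the pair. The delay since the last training cannot also be equal unless the control centre's e-learning is postponed, so the text should say which delay is held equal.
- Align the 1-month stagger, the 2-month training sequence and the movement in pairs with each other and with the schedule figures, and define T5 and T8 in the text.
- Recruitment began in September 2022, so for centres already past training, check the date collection opened against the date of the last simulation session.

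The cost is a change of wording or a small amendment. The downside is that the control centre of each pair waits some weeks longer before its post-training collection.
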